### Study objectives

The *primary objective* of the study is to determine the diagnostic
accuracy of the 4AT for delirium detection versus the reference standard of a DSM-IV
diagnosis.

The *secondary objectives* are:to compare performance of the 4AT and the CAM;to determine if the 4AT is an adequately sensitive tool for detecting
general cognitive impairment as judged against a documented history of
dementia and/or the Informant Questionnaire for Cognitive Decline in the
Elderly (IQCODE);to determine if 4AT scores predict important outcomes such as length of
stay, institutionalisation and mortality up to 12 weeks;to determine the performance of individual items of the 4AT,
for example, how accurate is altered level of alertness alone as a
predictor of delirium diagnosis?to assess the 4AT total score as a measure of delirium severity;to estimate the delivery costs of the 4AT and CAM as a function of their
diagnostic performance up to 12 weeks as well as modelling longer term
resource consequences.

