### Coding and recording assessments

The experimental assessments of delirium will be the 4AT and the CAM. The 4AT has a
total possible score of 12: items (1) and (4) can score 0 or 4 and items (2)
and (3) can score 0, 1 or 2.^12^ 4AT data will
be used for the primary objective as a binary outcome, with 0–3 scores giving
a ‘no delirium’ classification, and 4–12 scores giving a
‘delirium’ classification; for the secondary objectives, continuous
scoring, from 0 to 12, will be studied as a possible severity indicator, and scores
of 1–3 (indicating cognitive impairment but not delirium) can be studied
against other assessments of chronic cognitive impairment. The CAM will
be scored as delirium present or absent according to the algorithm. The 4AT,
CAM scoring and reference standard scoring will be recorded on a paper Case Report
Form.

Patient resource use will be derived from medical records, including the
‘TrakCare’ (InterSystems Corporation, Cambridge, Massachusetts, USA)
electronic patient record system, where available, as well as via patient or carer
self-report. The self-report resource-use questionnaire will include questions
regarding inpatient health and social care utilisation with a maximum recall period
of 16 weeks. The self-report resource-use questionnaire will be developed
specifically for the study for use by patient or proxy respondent using guidance from
the Database of Instruments for Resource Use Measurement.^50^ Administration of the questionnaire will be conducted at
12 weeks by one of the researchers in the study team, face to face where
patients are still hospitalised or via telephone. Data from the questionnaire will be
recorded on a paper Case Report Form.

The data on all the Case Report Forms will be transcribed into a secure database by
the researchers or a suitably qualified member of the research team. This will be
conducted using Edinburgh Clinical Trials Unit Standard Operating Procedures. Quality
checking will be performed in 10% of Case Report Forms.

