### Sample size calculation

Four hundred and fifty patients will be randomised to assessment by 4AT and 450 to
CAM. We will recruit sufficient patients to account for attrition, though we do not
expect significant attrition because the recruitment, consenting and assessment
process takes place over a small number of hours in a single episode. Of the 450
patients within each assessment arm, 15% (67) would be expected to have delirium. The
specificity of the triage tool would be estimated based on the 85% (383) without
delirium, while the sensitivity would be estimated from the 67 with delirium. Based
on the analysis using the normal approximation to the binomial distribution,
the two-sided 95% CI widths for the specificity and sensitivity would be as shown in
table 1 for a range of levels of diagnostic
test performance.

**Table 1 T1:** Precision of specificity, sensitivity estimation

Parameter	True level of parameter	95% CI width
Specificity	0.5	±0.050
Specificity	0.7	±0.046
Specificity	0.9	±0.030
Sensitivity	0.5	±0.120
Sensitivity	0.7	±0.110
Sensitivity	0.9	±0.072

It will therefore be possible to estimate the specificity precisely and the
sensitivity with moderate precision. The precision in estimating negative predictive
value would be expected to be similar to that for specificity; for positive
predictive value, it would be expected to be similar to that for sensitivity. For the
secondary objective of comparing 4AT and CAM, based on analysis by continuity
corrected χ^2^ test, we have 83% power to detect a difference in
specificity of 0.1, assuming a null hypothesis of specificity=0.70 for both
tests and a two-sided 5% significance level. The corresponding difference detectable
for sensitivity (null hypothesis sensitivity=0.7) would be 0.224 with 80% power.

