#### Secondary objectives

4AT versus CAM: differences in each of sensitivity, specificity, positive
and negative predictive values between 4AT and CAM will be tested by
Fisher’s exact test and quantified by the difference in the two
proportions (4AT-CAM) and its 95% CI. To aid comparison of 4AT and CAM, the
overall performance of each will also be summarised using Youden’s
Index (sensitivity minus false positive rate) and the OR of sensitivity to
specificity.Performance of the 4AT cognitive screening items: Is the 4AT an adequately
sensitive tool for detecting general cognitive impairment as judged against
a documented history of dementia and/or the IQCODE? This objective will be
addressed using the same methods as for the primary objective.4AT versus clinical outcomes: as assessment of criterion validity, we will
assess the performance of the 4AT in predicting length of stay,
institutionalisation and mortality up to 12 weeks. Descriptive
statistics of clinical outcomes will be presented for the groups with and
without 4AT scores above the cut point of 3. The relationship between 4AT
and each of mortality and institutionalisation will be analysed via logistic
regression modelling; Kaplan-Meier curves and the Cox proportional hazards
model will be used to assess 4AT as a predictor of hospital length of stay.
The logistic regression and Cox models will adjust for age, gender and
presence of dementia.Individual items: we will conduct analyses examining performance of
individual items of the 4AT, for example, is altered level of
alertness alone a good predictor of delirium diagnosis? (methods as per
primary objective);Delirium severity: we will assess the 4AT total score as a measure of
delirium severity by calculating the Spearman correlation between 4AT and
DRS-R98 scores and its 95% CI.

Full details of the proposed statistical analyses for the primary objective and
secondary objectives (a)–(e) will be documented in a SAP which will include
details of methods for calculating derived variables, any sensitivity and subgroup
analyses and approaches to testing the assumptions in the statistical analyses.
The SAP will outline the plan for validation of the statistical analysis.

Individuals with missing data for the reference diagnostic test will be removed
from formal statistical analysis. Where any items of the CAM or 4AT were not able
to be assessed, an overall delirium diagnosis will still be derived where possible

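### The delirium-severity objective rests on one 4AT/DRS-R98 correlation with no stated restriction to delirious patients, so as written it mixes severity with detection and with cognitive impairment in the non-delirious

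*Protocol article*

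**What the plan says.** Under Study objectives, one secondary aim is "to assess the 4AT total score as a measure of delirium severity". The Secondary objectives part of the Data analysis plan gives one method for it: "delirium severity by calculating the Spearman correlation between 4AT and" "DRS-R98 scores and its 95% CI". It names no population.

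Four other places bear on who would be analysed:

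- Coding and recording assessments describes the continuous score thus: "scoring, from 0 to 12, will be studied as a possible severity indicator, and scores" of 1–3 are then linked to chronic cognitive impairment. The same section classes 4AT scores of 0–3 as no delirium.
- The only exclusion stated with the analyses is general: "Individuals with missing data for the reference diagnostic test will be removed".
- Sample size calculation plans 450 patients for the 4AT and states that of these "15% (67) would be expected to have delirium", leaving 383 (85%) without it.
- Reference standard assessment makes DRS-R98 the centre of the assessment that leads to the delirium diagnosis.

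Details for the secondary objectives, including any subgroup analyses, are deferred to a SAP.

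**The concern.** Severity is a property of patients who have delirium. The 4AT is built to score higher in delirium. DRS-R98 is also higher there, the more so because it feeds the diagnosis. Pooling two groups that differ on both scores gives a positive correlation even if neither group has any internal association. The primary objective already measures that separation through sensitivity, specificity and the ROC area.

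Detection is not the only foreign component. Among patients without delirium, chronic cognitive impairment may raise both scores, and that is not delirium severity either.

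At stake is the reading of one secondary result: a clearly positive coefficient with a narrow interval could be taken as support for the 4AT total as a severity scale when it shows something else. The primary objective is unaffected.

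**Working it through.** **The plan's own figures.** 450 × 0.15 = 67.5 and 450 × 0.85 = 382.5, which agree with the stated 67 and 383. The Table 1 half-widths, 1.96 × √(p(1−p)/n), come to 0.0501, 0.0459 and 0.0300 for n = 383 and 0.1197, 0.1097 and 0.0718 for n = 67. All match. The article gives no figure for the Spearman analysis.

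**Inputs from the article.** Prevalence p = 0.15; n = 450; sensitivity 0.897 and specificity 0.841, from the Italian validation study described under Rationale for the study.

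**Assumptions, not in the article.**
- 4AT scores 0 to 3 split 55/20/15/10% among those below the cut point.
- 4AT scores 4 to 12 split 30/12/12/8/14/6/6/5/7% among those above it.
- DRS-R98 is normal with equal spread, the delirium groups being 1.5, 3 or 8 SD apart.
- p = 0.25 as an alternative prevalence.
- The two scores are independent within each delirium group, so the 4AT holds no severity information.

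**Formula.** Under that independence, whole-arm rho is the product of two correlations with delirium status D:

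- 4AT rank with D: √(p(1−p)) × d / SD(rank). Ranks are scaled 0 to 1, and d, the difference in mean rank, is (0.897 + 0.841 − 1)/2 = 0.369 here. The assumed splits give SD 0.278 at p = 0.15 and 0.281 at p = 0.25. The results are 0.357 × 0.369 / 0.278 = 0.473 and 0.433 × 0.369 / 0.281 = 0.568.
- DRS-R98 rank with D: √(12p(1−p)) × (AUC − 0.5), where AUC = Φ(separation/√2) = 0.856, 0.983 and 1.000.

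| Separation | p = 0.15 | Simulated | p = 0.25 | Simulated |
|---|---|---|---|---|
| 1.5 SD | 0.440 × 0.473 = 0.21 | 0.208 | 0.533 × 0.568 = 0.30 | 0.300 |
| 3 SD | 0.598 × 0.473 = 0.28 | 0.285 | 0.725 × 0.568 = 0.41 | 0.411 |
| 8 SD | 0.618 × 0.473 = 0.29 | 0.298 | 0.750 × 0.568 = 0.43 | 0.427 |

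The simulated columns are means over repeated 450-patient arms. In these scenarios the Fisher-z 95% interval lay above zero in at least 99.7% of runs. Within delirium, mean rho was about 0, and the interval lay above zero in 2–3% of runs.

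**Sensitivity to the assumptions.**
- Three other assumed 4AT distributions, with DRS-R98 means of 20 and 6, gave 0.28–0.35 at 15% and 0.41–0.48 at 25%.
- At sensitivity and specificity of 0.70 each and 15% delirium, rho was 0.11–0.16, with the interval above zero in 66–91% of runs.
- Raising true within-delirium rho from 0 to about 0.77 (0.897/0.841, 15%) moved whole-arm rho only from 0.21 to 0.26 at 1.5 SD, and from 0.29 to 0.30 at 3 SD.
- With no severity information but a modest association among the non-delirious (latent r = 0.3), whole-arm rho rose to 0.41–0.46.

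**Precision after restriction.** Fisher z with n = 67 has SE 1/√64 = 0.125. At rho = 0.5: tanh(0.549 ± 0.245) = 0.295 to 0.661. With the 1.03 factor sometimes used for Spearman, it is 0.289 to 0.665. At rho = 0 the half-width is 0.24, against 0.09 with n = 450. The rho detectable with 80% power is tanh((1.960 + 0.842)/8) = 0.34.

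**The case against.** The strongest reply is that the article is silent on the analysis set and does not declare one. It defers detail on the secondary objectives to a SAP, and the set for a secondary correlation could well be fixed there. This stands as a limit on certainty. It does not remove the point: the method that the article does state, followed literally, does not isolate severity.

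A reader might infer from the 0-to-12 range that the whole arm is meant. The text does not support that. The 0–3 class is the 4AT's own classification, and at a sensitivity of 89.7% about 10% of truly delirious patients would score there. The range fits a delirium-only analysis equally well. The exclusion for a missing reference standard is a general missing-data rule and settles nothing about this population.

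It is also fair that the article calls the score only a possible severity indicator and plans an estimate with an interval, with no test against zero and no success threshold. Nothing says that a rho of 0.3 would be called validation.

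Finally, restriction has a cost beyond width. Because DRS-R98 informs the diagnosis, its range is narrower among diagnosed patients. As an extreme illustration, under bivariate normality with diagnosis equal to the top 15% on DRS-R98, the DRS-R98 variance falls to 0.195 of its full value (SD ratio 0.441). A whole-range r of 0.6 then becomes 0.6 × 0.441 / √(0.64 + 0.36 × 0.195) = 0.31. A low within-delirium rho would therefore need careful reading, which is a reason to report both correlations.

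**Conclusion.** The concern holds in a limited form. The one analysis stated for delirium severity carries no restriction to delirious patients. Applied to the 4AT arm, it would combine detection, any association among the non-delirious, and severity. With no severity information at all, whole-arm rho would be about 0.2–0.35 at 15% delirium and about 0.3–0.48 at 25%. The higher prevalence is relevant because higher-risk patients were approached first in the last 5 months of recruitment (Identification of participants).

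The positive sign held in every scenario tried. The size rests on assumed score distributions and on accuracy taken from an earlier study. A reader might go further and conclude that the 4AT holds no severity information, or that the trial will claim a validated severity scale. Neither follows: the zero within-delirium correlation is a premise of the check, and the article sets no rule for such a claim. The SAP may already contain the delirium-only estimate.

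**What to change.** State in the SAP that the estimate bearing on delirium severity is the Spearman correlation, with 95% CI, between 4AT total and DRS-R98 among 4AT-arm patients with reference-standard delirium. Report the whole-arm correlation alongside it, labelled as reflecting detection plus severity.

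This takes a sentence or two and no new data. The costs are the wider interval (n about 67) and the attenuation from the narrower DRS-R98 range. Both should be stated when the result is interpreted. If the SAP already specifies this, it need only make clear which of the two correlations addresses the objective.

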### Study oversight

Study oversight is through the trial steering committee, which will meet every
4 months during the study. The trial steering committee comprises two
independent lay representatives, three independent experts (one of whom is the Chair
of the committee), the principal investigator (PI), the study statistician and
representatives from the Edinburgh Clinical Trials Unit.

### Data protection

Data will be collected and handled in line with sponsor and Edinburgh Clinical Trials
Unit Standard Operating Procedures and NHS Trust policies. All electronic data will
be link anonymised.

## Discussion

This study was designed to validate the 4AT against a reference standard assessment, as
well as compare it with another commonly used test for assessment of delirium. Since the
initial study design, the 4AT has been widely adopted nationally and internationally.
The 4AT has been incorporated into routine practice in multiple international centres,
both in paper and electronic format, with many centres reporting 10 000 uses of
the tool. The website www.the4AT.com has had an increasing degree of traffic, and the 4AT has
been translated into multiple languages. The 4AT is also included in several national
guidelines and position statements internationally as a recommended tool and it has been
validated in other studies^38–42^ but it is still essential that it is further tested in a large
study. It is also essential to consider how well it identifies other types of cognitive
impairment, relates to future outcomes and its health economic impact.

In the initial design and implementation of the study, the main challenging aspects have
been: (1) considering both Scottish and English legal and ethical framework to ensure
that patients without capacity are included. Ethical approval for inclusion of these
patients was granted though recruitment of this patient group proved difficult from the
outset for several reasons. First, the narrow boundaries for the screening and
identification strategy. This was addressed in a subsequent protocol amendment to aim
for oversampling of patients at risk of developing delirium. Second, the availability of
an appropriate individual to provide consent on behalf of the participant (ie, a
personal or nominated consultee, guardian, welfare attorney or nearest relative). Third,
a reluctance to consent due to perceived burden on participant. Persuading relatives of
the value, importance and necessity of research even in clinically unwell patients
demands a particular skillset from researchers and involved perseverance and excellent
communication in order to achieve recruitment targets.

(2) Recruitment and training of staff, with some staff moving to different posts,
and new staff being recruited and requiring training; in each case, detailed training
supported by reading materials and practice sessions was provided.

We also acknowledge that it is possible that researcher bias may influence how the
different index assessments (4AT or CAM) were scored. We also acknowledge that given the
fluctuating nature of delirium, the gap between assessments potentially reaching
2 hours means that assessments could have different findings. We will conduct
sensitivity analyses to analyse the impact of variations in the time gap between
assessments.

## Conclusion

The 4AT study aims to assess the validity of this rapid delirium screening tool that can
be administered by a range of professional- level healthcare staff to patients with
sensory or functional impairments in a busy clinical environment, which also
incorporates general cognitive assessment. We will also assess the later functional
outcomes of people with and without delirium and the health economic implications. The
overall aim is to improve detection, and therefore management and outcomes, of this
important and devastating condition.
